| IRB Institute
IRB Number | Human Research Ethics Committee, University of Cape Town
HREC 243/2022                                                                                                                                                                                                                                                                                                                                                                                                                  |
| Clinicaltrials.gov                 | NCT05610098                                                                                                                                                                                                                                                                                                                                                                                                                                                                                |
| Proposed dates                     | Start: September 2022    End: December 2025                                                                                                                                                                                                                                                                                                                                                                                                                                                |
| Recruitment target                 | Screening:            120                      Enrolment: 100
Follow-up:            12 months                                                                                                                                                                                                                                                                                                                                                                                           |

## Study overview (Synopsis)

|                   |                                                                                                                                                                                                                                                                                                                                                                                                                                                                                                                                                                                                                                                                                                                                                                                                                                                                                                                                                                                                                                                                                                                                                                                                                                                                                                                                                                                                                                                                                                                                                                                                                                                                                                                                                                                                                                                                                                        |
|-------------------|--------------------------------------------------------------------------------------------------------------------------------------------------------------------------------------------------------------------------------------------------------------------------------------------------------------------------------------------------------------------------------------------------------------------------------------------------------------------------------------------------------------------------------------------------------------------------------------------------------------------------------------------------------------------------------------------------------------------------------------------------------------------------------------------------------------------------------------------------------------------------------------------------------------------------------------------------------------------------------------------------------------------------------------------------------------------------------------------------------------------------------------------------------------------------------------------------------------------------------------------------------------------------------------------------------------------------------------------------------------------------------------------------------------------------------------------------------------------------------------------------------------------------------------------------------------------------------------------------------------------------------------------------------------------------------------------------------------------------------------------------------------------------------------------------------------------------------------------------------------------------------------------------------|
| Title      | Comparing gene expression profiles of adult patients with isolated spinal TB to disseminated spinal TB identified by  FDG-PET/CT at time of diagnosis, 6- and 12-months follow-up                                                                                                                                                                                                                                                                                                                                                                                                                                                                                                                                                                                                                                                                                                                                                                                                                                                                                                                                                                                                                                                                                                                                                                                                                                                                                                                                                                                                                                                                                                                                                                                                                                                                                                         |
| Summary    | 
Tuberculosis (TB) is one of the top ten causes of death worldwide with approximately 10 million cases globally and 1.2 million deaths. Sub-Saharan Africa carries the highest burden of TB. South Africa has one of the highest HIV and TB rates worldwide with an HIV prevalence rate in adults of 19% and a TB case notification rate of 615/100,000 in 2019. Over many years, focus has been paid to pulmonary TB and extrapulmonary TB (EPTB) has received only little attention even though it accounts for almost a quarter of all TB cases. The diagnosis of EPTB remains challenging simply because sample collection requires invasive procedures in the absence of a blood-based diagnostic test. Spinal TB (spondylitis or spondylodiscitis caused by Mycobacterium tuberculosis) - often known as Pott's disease - accounts for up to 10% of EPTB and affects young children, people with HIV-coinfection and elderly, and often leads to lifelong debilitating disease due to devastating deformation of the spine and compression of neural structures. Little is known with regards to the extent of disease and isolated TB spine as well as a disseminated form of TB spine have been described. The latter presents with a spinal manifestation plus disseminations to other organs such as the lungs, pleura, lymph nodes, the GIT or urinary tract or even the central nervous system.
 
In our Spinal TB X cohort, we aim to describe the clinical phenotype of spinal TB using whole body PET/CT and identify a specific gene expression profile for the different stages of dissemination and compare our findings to previously described signatures for latent and active pulmonary TB. A blood-based test for spinal TB would lead to earlier diagnosis and treatment in all settings globally and improve treatment outcome of this devastating disease.
 |
| Hypothesis | 
1. We hypothesize that spinal TB may present as two clinical phenotypes: isolated spinal TB with no additional lesion on whole body PET/CT and disseminated spinal TB with a spinal lesion plus an additional extraspinal lesion on whole body PET/CT.
 
2. We hypothesize that a specific gene expression profile may distinguish between the two clinical entities above and allows for treatment monitoring during antimicrobial therapy ("personalized medicine")
 
3. We hypothesize that whole body PET/CT is superior to MRI in diagnosing spinal and extraspinal TB.
                                                                                                                                                                                                                                                                                                                                                                                                                                                                                                                                                                                                                                                                                                                                                                                                                                                                                                                                                                                                                                                                                                                                                                                                                                                                                                          |
| Objectives | 
Primary objective
 
To describe the clinical phenotype of spinal TB using whole body PET/CT and to identify mRNA gene expression profiles of isolated spinal TB versus disseminated spinal TB stratified by HIV status.
 
Secondary objectives
 
 
1. To identify the distributive patterns of suspected spinal TB using two imaging modalities: MRI and PET/CT.
 
2. To analyse the genomes of Mtb. extracted from different sites of the body (if available) and to identify differences in their genome regarding SNPs and drug susceptibility.
 
3. To analyse imaging findings using PET/CT at treatment initiation, 6 months, and 12 months to better understand treatment outcome using PET/CT.
 
4. To compare imaging findings on PET/CT and MRI at baseline to evaluate the role of PET/CT in spinal TB diagnostics (virtual biopsy).
 
                                                                                                                                                                                                                                                                                                                                                                                                                                                                                                                                                                                                                                                                                                                                                                                                                                                                                                                                               |

|                                   |                                                                                                                                                                                                                                                                                                                                                                                                                                                                                                                                                                                                                                                                                                                                                                                                                                                                                                                                                                                                                                                       |
|-----------------------------------|-------------------------------------------------------------------------------------------------------------------------------------------------------------------------------------------------------------------------------------------------------------------------------------------------------------------------------------------------------------------------------------------------------------------------------------------------------------------------------------------------------------------------------------------------------------------------------------------------------------------------------------------------------------------------------------------------------------------------------------------------------------------------------------------------------------------------------------------------------------------------------------------------------------------------------------------------------------------------------------------------------------------------------------------------------|
| Design                     | This is a prospective cohort study to develop new diagnostic biomarkers for isolated spinal TB versus disseminated spinal TB and treatment monitoring. Furthermore, this study investigates Mtb. strain variations in spinal TB in relation to its distributional pattern. After MRI-confirmation of spinal TB according to local algorithms, patients will be invited to join the study. At baseline, clinical examination as well as blood biobanking will be performed. Every patient with unknown HIV status will undergo HIV-testing. Sputum will be collected for Mtb. culture and GeneXpert as well as specimens from other sites of TB disease (e.g. urine, FNA) and screening for diabetes and pregnancy will be performed. Whole-body PET/CTs will be performed at time of diagnosis (0 month), 6 months, and 12 months of treatment. Either spinal biopsies or surgery will be performed according to clinical indication to confirm the diagnosis of spinal TB at baseline after imaging modalities have been performed (MRI and PET/CT). |
| Population                 | Patients with newly diagnosed spinal TB at Groote Schuur Hospital and its affiliated hospitals, UCT Private Academic Hospital and other private hospitals in the region.                                                                                                                                                                                                                                                                                                                                                                                                                                                                                                                                                                                                                                                                                                                                                                                                                                                                              |
| Participant Duration       | Approximately 12 months                                                                                                                                                                                                                                                                                                                                                                                                                                                                                                                                                                                                                                                                                                                                                                                                                                                                                                                                                                                                                               |
| Time to complete enrolment | Approximately 2 years                                                                                                                                                                                                                                                                                                                                                                                                                                                                                                                                                                                                                                                                                                                                                                                                                                                                                                                                                                                                                                 |

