### 3 Study Hypothesis and Objectives

#### Hypothesis

1. We hypothesize that spinal TB may present as two clinical phenotypes: isolated spinal TB with no additional lesion on whole body PET/CT and disseminated spinal TB with a spinal lesion plus an additional extraspinal lesion on whole body PET/CT.
2. We hypothesize that a specific gene expression profile may distinguish between the two clinical entities above and allows for treatment monitoring during antimicrobial therapy ("personalized medicine")
3. We hypothesize that whole body PET/CT is superior to MRI in diagnosing spinal and extraspinal TB.

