#### Primary objective

To describe the clinical phenotype of spinal TB using whole body PET/CT and to identify and mRNA gene expression profiles of isolated spinal TB versus disseminated spinal TB stratified by HIV status.

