## 4.2 Participant characteristics

Participants with clinically and MR-suspected spinal TB will be recruited from Groote Schuur Hospital, Cape Town, South Africa, its affiliated hospitals, UCT Private Academic Hospital and other private hospitals in the region. According to the current caseload, we will be able to include 50 participants per year, aiming for 100 participants in total. However, if recruitment goals cannot be achieved according to aim, Tygerberg Hospital, Cape Town, South Africa may be approached to enhance recruitment. In result, we are aiming for 300 PET/CTs (100 initial, 100 at 6 months, 100 at 12 months) and 300 peripheral blood samples for gene expression analysis.

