## **6.13 Analysis**

Analysis will be performed using SPSS®. Continuous data will be analysed as median and interquartile range [IQR] and categorical data as frequencies (%) with their 95% confidence interval (CI) where appropriate. For comparing proportions between two groups, we use the chi-square (v2) test. Medians will be compared between two groups (HIV infected and HIV uninfected) using the Wilcoxon ranksum test. Univariate logistic regression will be performed and the cut-off P-value < 0.2 used for inclusion of variables in the multivariate logistic regression model. Multivariate logistic regression will use a stepwise backwards and manual intelligent techniques to identify the independent predictors of the composite endpoint of MS. The logistic regression models' results will be presented as odds ratios (OR) with the 95% CI. Statistical significance will be accepted at the two-sided level of  $P \leq 0.05$ . Sociodemographic and clinical data as well as laboratory findings will be analysed.

Semiquantitative PET/CT analysis will be performed using MIM® Software. Total lesion glycolysis (TLG) at the region of interest (ROI) will be measured as well as SUVmean, SUVmax and SUVvolume after subthreshold calculation of the ROI.

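### The aim is a diagnostic profile that tells isolated from disseminated spinal TB, but the inferential methods in section 6.13 neither measure discrimination nor take that contrast as their outcome

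*Protocol*

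**What the plan says.** The Synopsis describes the design as "This is a prospective cohort study to develop new diagnostic biomarkers for isolated spinal TB versus disseminated spinal TB and treatment monitoring", and section 4.1 repeats this. Hypothesis 2 (Synopsis and section 3) expects that "a specific gene expression profile may distinguish between the two clinical entities above", meaning isolated and disseminated spinal TB as seen on whole-body PET/CT. The primary objective concerns "mRNA gene expression profiles of isolated spinal TB versus disseminated spinal TB stratified by HIV status". On size, section 4.2 says "we will be able to include 50 participants per year, aiming for 100 participants in total"; the basis is caseload.

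Section 6.13 is the protocol's only analysis section. It lists:

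- descriptive summaries: medians with IQR, frequencies with 95% CI, and PET/CT uptake measures;
- a chi-square test for proportions in two groups that it does not name;
- a rank-sum test between HIV-infected and HIV-uninfected participants;
- univariate logistic screening at P < 0.2, followed by backward and manual selection, to find predictors of a composite endpoint labelled MS, a term the protocol does not define.

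On reporting it says "The logistic regression models' results will be presented as odds ratios (OR) with the 95% CI". On the decision rule it says "Statistical significance will be accepted at the two-sided level of" P ≤ 0.05. It does not mention gene expression or the isolated-versus-disseminated contrast.

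**The concern.** Developing a diagnostic marker that distinguishes two entities is a question of discrimination: how well the profile sorts patients into the two groups. The inference in 6.13 is about association. An odds ratio that differs from 1 shows that the groups differ on average, which is compatible with heavy overlap between them. The size of an odds ratio also depends on the unit of expression (per cycle threshold, per log2, per SD), so odds ratios on different scales cannot rank genes or signatures as diagnostics.

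There is a second mismatch. The outcome of the multivariable model and the grouping of the rank-sum test are not the contrast named in the design, in hypothesis 2 or in the primary objective.

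At stake is the study's main translational claim. Applied as they stand, the methods in 6.13 give no estimate of how well a profile separates the phenotypes. If they were simply redirected to the right outcome, a significant result would still say little about diagnostic value.

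**Working it through.** **Aim against method**

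| Item | Stated aim | Section 6.13 |
|---|---|---|
| Contrast | isolated v disseminated | MS endpoint (logistic model); HIV groups (rank-sum); groups not named (chi-square) |
| Marker | gene expression profile | not mentioned |
| Measure | ability to distinguish | odds ratio with 95% CI |
| Criterion | none stated for the profile | two-sided P ≤ 0.05 |

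The rank-sum statistic can be rescaled to an AUC, but 6.13 uses it to compare medians between HIV groups.

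**How weak can a significant profile be?** The protocol states no power, effect size or AUC, so it has no figure of its own to reproduce. Suppose the analysis were pointed at isolated versus disseminated, with one score fixed beforehand.

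Inputs: N = 100 (section 4.2) and two-sided 0.05, z = 1.96 (section 6.13). The phenotype split and an HIV stratum of 50 are assumptions.

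The smallest AUC reaching P ≤ 0.05, from the Mann-Whitney null variance, is

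AUC = 0.5 + 1.96 × √[(n1 + n2 + 1) / (12 × n1 × n2)].

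At 50/50: 0.5 + 1.96 × √(101 / 30,000) = 0.5 + 1.96 × 0.0580 = 0.614.

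At 10/90: 0.5 + 1.96 × √(101 / 10,800) = 0.5 + 1.96 × 0.0967 = 0.690.

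| Setting (assumed split) | Mann-Whitney | t-test, binormal | Hanley-McNeil SE |
|---|---|---|---|
| 100: 50/50 | 0.614 | 0.611 | 0.610 |
| 100: 30/70 | 0.624 | 0.620 | 0.623 |
| 100: 20/80 | 0.642 | 0.637 | 0.643 |
| 100: 10/90 | 0.690 | 0.680 | 0.690 |
| HIV stratum of 50: 25/25 | 0.662 | 0.656 | 0.652 |
| HIV stratum of 50: 15/35 | 0.676 | 0.670 | 0.671 |
| HIV stratum of 50: 10/40 | 0.702 | 0.692 | 0.697 |

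A 5/45 split within a stratum would need 0.75 to 0.77, so the stratum range of about 0.65 to 0.70 covers splits from 25/25 to 10/40.

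A logistic check at 50/50 agrees. The Wald SE of the log odds ratio per SD is about 1/√(100 × 0.5 × 0.5) = 0.20, so the just-significant value is 1.96 × 0.20 = 0.392. That is an odds ratio of 1.48 per SD. For an equal-variance normal score, AUC = Φ(0.392/√2) = 0.609 and equal sensitivity and specificity = Φ(0.392/2) = 0.578. In simulated 50/50 logistic fits, the 101 data sets with P between 0.04 and 0.05 had a mean AUC of 0.615 and a mean odds ratio of 1.52. Sensitivity and specificity near 0.58 mean that about 42% are misclassified at that cut-off.

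**Precision if the AUC were the output.** With the Hanley-McNeil SE and a true AUC of 0.80, Q1 = 0.80/1.20 = 0.6667 and Q2 = 2 × 0.64/1.80 = 0.7111.

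- 50/50: SE = √[(0.16 + 49 × 0.0267 + 49 × 0.0711)/2500] = 0.0445, half-width 1.96 × 0.0445 = 0.087.
- 25/25: SE = √[(0.16 + 24 × 0.0267 + 24 × 0.0711)/625] = 0.0633, half-width 0.124.
- 20/80: half-width 0.123.

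These treat the score as fixed. Selecting genes in the same data adds variability.

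**The case against.** A reader might infer that, under this plan, a profile misclassifying about 4 in 10 participants would be accepted as a successful diagnostic biomarker. The documents do not support that. Section 6.13 never applies its odds ratios or its P value to the gene profile, and no section says that a significant odds ratio makes a profile a biomarker. Section 6.5 leaves the host mRNA analysis to a third-party company, another academic group or the South African MRC. Nor are odds ratios and P values the only outputs, since 6.13 also lists descriptive summaries and PET/CT measures.

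It can also be said that AUC, cross-validation and cut-offs commonly belong in a statistical analysis plan, which may exist and is not shown here. Their absence alone is indeed no finding. What stands is that 6.13 commits to specific outcomes, groupings, outputs and a significance rule, and these do not fit the stated aim. A later plan that added an AUC would leave that text in place.

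The wording of the aim is exploratory: the primary objective is to describe and identify, and hypothesis 2 says may. That argues against reading a firm accuracy claim into the protocol. It does not make association measures suitable for a marker meant to distinguish.

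Finally, any test on 100 people becomes significant at a modest effect, and 0.61 is the low end of the range. Both are true. The calculation illustrates why P ≤ 0.05 is a poor yardstick for discrimination; it does not show an arithmetical error in the plan.

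**Conclusion.** The point holds in this form: the inferential methods in 6.13 do not measure discrimination, and none is written for isolated versus disseminated disease, although both are central to the design and hypothesis 2. Correcting the outcome alone would leave a criterion that a weak classifier can meet. The just-significant AUC is about 0.61 for 100 evaluable participants split 50/50, about 0.69 at 10/90, and about 0.65 to 0.70 within an HIV stratum of 50 split between 25/25 and 10/40. These figures assume a single pre-specified score; the sensitivity, specificity and odds ratio per SD also assume an equal-variance normal score. The mismatch between aim and method is read directly from the text and does not depend on these assumptions.

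**What to change.** In section 6.13, state that the part of hypothesis 2 about distinguishing the phenotypes is assessed with isolated versus disseminated as the outcome. Use the cross-validated AUC of the gene expression profile with its 95% CI, repeating gene selection inside each fold. Add sensitivity and specificity at a cut-off set beforehand. Report these for the whole cohort and, descriptively, by HIV status. Keep odds ratios as description only. Either define the MS endpoint and say which question it serves, or remove it.

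Whether to require a minimum AUC, and at what value, is for the sponsor to decide in advance. For a true AUC of 0.80, the expected lower 95% limit is about 0.80 − 0.09 = 0.71 at 50/50 and about 0.80 − 0.12 = 0.68 in a 25/25 HIV stratum. A floor that is workable for the whole cohort may therefore be out of reach within a stratum.

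The cost is a change to the text of 6.13 and a little more analysis of data already being collected. The headline may be less favourable than a significant odds ratio.
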